### Inclusion criteria

Participants are included according to the following criteria: 1) a confirmed diagnosis of stroke, defined as the presence of symptoms persisting beyond 24 hours and/or a positive CT scan, one month previously; 2) no pre-existing neurological condition, psychiatric condition or chronic drug/alcohol abuse known to affect emotion processing; 3) no severe cognitive impairment (MMSE score >23).

### Measures

The following measures will be used at both the one-month post-stroke and one-year post-stroke assessments:

### Emotion processing measures

#### Emotion perception

There are several ways in which we gather cues as to other people’s emotions; from their facial expressions of emotions, from their voice through the emotional intonation within their speech. Previous research has suggested that the accurate perception and integration of all these cues are used in order to accurately infer what higher order emotions are being conveyed [13]. All three of these cues will be examined. To assess emotion perception in the visual modality the standardised Facial Expressions of Emotion: Stimuli and Test [34](Young, Perrett, Calder, Sprengelmeyer & Ekman, 2002) will be administered. This forced-choice paradigm requires participants to look carefully at static pictures of faces and choose which word best describes the emotion expressed in each picture from a provided list of six emotions; happy, sad, anger, disgust & fear.

In order to assess emotion perception ability in the auditory modality, a sub-test of the Florida Affect Battery [35] (Bowers, Blonder, Slomine & Heilman, 1996) will be administered. The emotion labelling task involves the presentation of one spoken sentence in an emotional tone. The participant then chooses from a list of words which emotion word best characterised the emotional intonation of the voice.

As we rarely view faces in isolation, or judge emotion on voice alone, a more ecologically valid measure of emotion perception has also been incorporated into the test battery. The Awareness of Social Inference Test [14], comprises 28 videoed vignettes of actors engaged in everyday situations in which they experience one of seven emotional states (happy, surprised, angry, sad, disgusted, anxious, and neutral) which the participant has to identify. The scripts in all cases are ambiguous in content. This measure is of particular importance as it has been established to have ecological validity with failure to recognise cues on TASIT translating into observable and reliable difficulties in spontaneous social situations [14], however as it has rarely been used in stroke populations before, this measure is administered in combination with the established measures described.

#### Emotion regulation

The methods by which emotions are regulated is dependent on several different factors, and so several areas of emotion regulation will be assessed, including the awareness and understanding of the emotion experienced; acceptance of the emotion; an ability to control impulsivity ensuring that one’s behaviour fits the desired goals even when experiencing negative emotions; and an ability to use flexible strategies to regulate emotional experience. Emotion regulation strategies will be assessed using the Difficulties in Emotion Regulation Scale (DERS) [36]. The DERS is a brief, 36-item, self-report questionnaire designed to assess multiple aspects of emotion dysregulation, including *nonacceptance* of emotions, *impulse* control of emotion, *awareness* of emotions, *strategies* of emotion regulation, ability to achieve desired *goals* and *clarity* of emotion.

#### Anxiety and depression

Depression and anxiety are common consequences of stroke, which have been shown to impact on other aspects of emotion processing as well as our desire to engage in social activities and contact. Two measures of depression and anxiety are to be administered. The first measure is the extensively used and validated Hospital Anxiety and Depression Scale [37] which has been shown to measure anxiety and depression, without confounding by physical symptoms. A further measure of depression the Centre for Epidemiological Studies Depression scale (CES-D) [38] will also be administered.

#### Social participation measures

Social Participation will be assessed in terms of several domains of engagement in social situations, including recreation, work, home activities, social aspects of life, as well as frequency of social contacts and networks. The Modified Functional Limitation Profile (mFLP) [39] will be administered. This is a hierarchical measure of participation, with 136 items giving scores across 12 categories. The categories established to assess social participation are those of; mobility, household, recreation, social interaction and work (Johnston & Pollard, 2001).

The World Health Organisation Quality of Life measure (WHO-QoL BREF) [40] is a multidimensional measure of quality of life, separated into four domains; physical health, psychological, social relationships and environmental. The WHO-QoL BREF has been shown to measure participation, and 80% of the WHO-QoL items have been demonstrated to tap some aspect of social participation [41] with 42% of those items purely measuring social participation. This measure specifically asks an individual about their *satisfaction* with their ability across the four domains.

Size of participants’ social networks will be assessed using the Lubben Social Network Scale (LSNS-18) [42]. This measure uses 18 questions which evaluate the size of different aspects of social network that are attributable to family ties, friendship ties and neighbourly ties. The LSNS-18 assesses the size of the respondent’s active social network (i.e., relatives or friends seen or heard from ≥1 times/month), perceived support network (i.e., relatives or friends who could be called on for help), and perceived confidant network (i.e., relatives or friends to whom the respondent could talk about private matters). Both the Lubben Social Network scale and the WHO-QoL BREF have been shown to measure participation as defined by the ICF [43].

### Activity limitation

The Modified Functional Limitation Profile (mFLP) [39] categories measuring activity limitation are those of ambulation, body care, alertness and communication.

### Impairment

Cognitive impairment will be assessed to provide a basic screen using the Mini Mental State Examination (MMSE) [44]. A score of less than 23 will result in the patient being excluded from the study.

### Procedure

Consecutive recruitment will be employed with potentially eligible participants identified from the stroke units and clinics. Participants are invited to participate in the study by letter from the lead clinician. Participants on the ward are given the letter, a participant information sheet and a reply form, and may then put their reply form in a box provided at the nurse’s station on the ward if they wish to participate. Participants discharged to home receive the same letter, information sheet and reply form posted to their home with a freepost envelope to post their reply form back to the researcher if they wish to participate. Participants who consent are required to complete two sessions, each session lasting approximately one and a half to two hours. The first session is to occur at approximately one month post stroke and the second session is to occur at approximately one year post stroke. All measures are administered at both time points. Participants can opt to split each session into multiple sessions should they wish to, to ensure that participants do not become fatigued. Participants can be assessed on the ward, in their home or at the University of Aberdeen.

### Ethical status and considerations

The North of Scotland Research Ethics committee have given a favourable ethical opinion for the study protocol, REC Number 08/S0802/8, and recruitment has commenced. Written informed consent is obtained from each participant as set out by the local ethical review board. No risk is associated with any of the measures to be used. All questionnaires being used are standardised and validated and have been used in previous studies with similar populations. Taking part in this study may involve minor inconvenience for the participants, in terms of spending time taking part in the assessments and in some instances travel to testing sessions. However, in a bid to alleviate the latter inconvenience participants will be given the option of the researcher attending their home or hospital ward. Any expenses that the participants incur will be reimbursed.

### Sample size

The sample size was calculated using a G-Power statistical sample size calculation. For F tests with a medium effect size, with an error probability of 0.05 and power of 0.95 the total sample required is 119.

### Analysis

Initially, a correlational analysis will be conducted on the measures from each domain of emotion processing to ascertain if the measures within that domain are highly correlated with each other. If this is the case the measures will be amalgamated. The same process will be conducted with the measures of social participation. Should the measures not be highly correlated an exploratory factor analysis will be conducted.

Regression analyses will be conducted to investigate whether the emotion processing measures predict social participation measures, controlling for activity limitations. The final research question was whether emotion processing deficits in the acute phase of stroke predict social participation at one year post stroke which is not accounted for by activity limitation? To address this, hierarchical regression analyses will be conducted, predicting social participation at second assessment from concurrent activity limitation in the first step and emotion processing from the acute phase of stroke entered in the next step of the regression.

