## Discussion

### Potential implications of work

This project will address a number of health care service priorities, including stroke, mental health, ageing and quality of life. This research has the potential to improve knowledge of the effects of stroke on mood and emotion perception, as well as enhancing our knowledge of the relationship between emotion processing constructs and participation outcome. Improving our understanding of the emotional factors which may underlie key social deficits in stroke is important to inform models of functioning and disability following stroke, as factors other than activity and cognitive limitations may be important in influencing post-stroke outcomes.

The results from these studies will be of interest not only to the academic community with an interest in ageing and health outcomes, but also to both medical groups and patient support groups with an interest in stroke. In the longer term, the results from this study may influence future practice within rehabilitation settings. If emotion processing difficulties predict participation levels and activity limitation, then those individuals could potentially be targeted for intervention in the acute stroke phase, ensuring that rehabilitation potential is fulfilled. Interventions have previously been successful in improving recovery in stroke patients. A randomised controlled trial of an intervention to increase patients’ perceived control over their recovery resulted in better recovery from activity limitations [45]. Interventions targeting emotional states in the acute phase of stroke have been found to improve quality of life outcomes [30]. This research is also important in combining theoretical and applied scientific approaches from health psychology and cognitive neuroscience to important health problems.

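### The regressions adjust only for activity limitation, so cognition may confound the link between emotion-perception scores and participation, although MMSE is collected at both visits

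*Protocol article*

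**What the plan says.** All references are to the protocol article.

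- **Models (Analysis).** "Regression analyses will be conducted to investigate whether the emotion processing measures predict social participation measures, controlling for activity limitations". For research question 3 the steps are given: "predicting social participation at second assessment from concurrent activity limitation in the first step and emotion processing from the acute phase of stroke". Neither statement includes a cognitive term.
- **Role of the MMSE (Impairment).** "Cognitive impairment will be assessed to provide a basic screen using the Mini Mental State Examination (MMSE"). No other use is described.
- **Entry rule.** Inclusion criteria: "no severe cognitive impairment (MMSE score >23"). Impairment: "A score of less than 23 will result in the patient being excluded from the study".
- **Timing (Procedure).** "All measures are administered at both time points". The MMSE is listed under Measures, so a one-month and a one-year score should exist.
- **Content of the one covariate (Activity limitation).** The mFLP "categories measuring activity limitation are those of ambulation, body care, alertness and communication".
- **Rationale (Potential implications of work).** The work is motivated by the possibility that "factors other than activity and cognitive limitations may be important in influencing post-stroke outcomes".

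**The concern.** The three emotion-perception measures (faces, spoken sentences, video vignettes) are performance tests. The participant has to attend to a stimulus, understand it and choose a verbal label. Scores therefore plausibly depend on attention, language and memory as well as on emotion perception. The article's Stroke section itself lists language and memory among the functions that stroke can impair. Poorer cognition can also reduce social participation directly. If so, it is a common cause of a low perception score and low participation, and a model without it credits part of its effect to emotion perception.

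This matters because the article goes beyond forecasting. The Aims ask how emotion impairments affect participation and say that the longitudinal design allows causal direction to be explored. The Discussion looks ahead to intervening in the acute phase on people with emotion-processing difficulties. If the association were largely cognitive, that would be the wrong target.

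**Working it through.** **1. What already controls for cognition**

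- *Restriction.* The MMSE rule removes low scorers, but all variation above the cut-off stays in the sample.
- *Proxy covariate.* Two of the four activity-limitation categories, alertness and communication, may overlap with cognition. They rate functional limitation and are not a cognitive test. For question 3 the activity-limitation score is the one-year score, while the emotion tests are taken at one month. The proxy is therefore not measured when the perception scores are obtained.

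Both controls are real, and both are partial.

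**2. The plan's own sample size**

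Inputs from the Sample size section: F test, medium effect, error probability 0.05, power 0.95, N = 119. Two inputs are not stated and are assumed: f² = 0.15 for a medium effect in regression, and three tested predictors (the three emotion constructs).

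Power = P(F′ > F critical), where F′ is noncentral F with u tested terms, N − p − 1 denominator degrees of freedom (p = all predictors) and noncentrality f² × N.

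For u = 3 the noncentrality is 0.15 × 119 = 17.85. Power at N = 119 is 0.951, and 119 is the smallest N reaching 0.95. The stated figure is reproduced. One, two, four or five tested predictors would need 89, 107, 129 or 138.

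**3. Cost of adding MMSE** (u = 3, same f²)

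| Model | p | Denominator df at N = 119 | Power, N = 119 | Power, N = 125 |
|---|---|---|---|---|
| Activity limitation + 3 emotion terms | 4 | 119 − 4 − 1 = 114 | 0.9509 | 0.9605 |
| The same + MMSE | 5 | 119 − 5 − 1 = 113 | 0.9508 | 0.9605 |

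The required N stays 119. These figures hold f² fixed. If adjustment shrinks the emotion effect, that shrinkage is the confounding being removed.

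**4. Illustration of the bias (assumed values only)**

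Suppose emotion has no true effect. Given activity limitation, let cognition correlate r with the perception score and have a standardised effect g on participation. Leaving cognition out gives a spurious emotion coefficient b = r × g, with f² = b² / (1 − b²). The documents give neither r nor g. The ranges assumed are r = 0.2 to 0.5 and g = 0.2 to 0.4.

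| r | g | b | f² | Rejection, 1 df (p = 2), N = 119 | Rejection, 3 df (p = 4), N = 119 |
|---|---|---|---|---|---|
| 0.2 | 0.2 | 0.04 | 0.0016 | 7% | 6% |
| 0.3 | 0.3 | 0.09 | 0.0082 | 17% | 11% |
| 0.5 | 0.3 | 0.15 | 0.0230 | 37% | 25% |
| 0.5 | 0.4 | 0.20 | 0.0417 | 60% | 42% |

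The 1-df column tests one perception term alone. The 3-df column tests three emotion terms jointly, with the spurious part in one of them. Truncation of MMSE at entry would tend to pull r and g towards the lower rows.

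**The case against.** The strongest reply is that the models match the question asked. The abstract, the Aims and research question 3 all speak of independence from activity limitation and do not name cognition. The Design section calls the study predictive, and for pure prediction an omitted correlate is not a bias. Low MMSE scorers are excluded, and the activity covariate includes alertness and communication. The MMSE is a brief screen with a truncated range, so adding it would not settle the matter. A fuller analysis plan may also contain further covariates.

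Much of this stands, and it rules out three stronger readings that a reader might infer:

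- *That the plan promises a finding beyond cognitive limitations and then fails to test it.* The sentence in Potential implications of work is a hedged reason for doing the study. It is not a conclusion the study undertakes to draw, so there is no internal contradiction.
- *That emotion and cognition cannot be separated at all.* The entry rule and the mFLP categories separate them in part.
- *That every emotion measure is affected alike.* The mechanism concerns the perception tests. The DERS, HADS and CES-D are self-report scales, to which it applies less directly.

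Two parts of the reply do not stand. The prediction argument fails because the Aims speak of impact and causal direction. The condensed-article argument is weak because the covariate and the model steps are written out, so this is a stated choice.

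**Conclusion.** The point holds in a limited form. Every model the article specifies leaves out cognition, although a measure of it is collected at both visits, and cognition is a plausible confounder of the association between perception scores and participation. Existing controls are partial. The stated aim can still be answered, but a positive result for the perception tests would be harder to interpret.

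The size is illustrative. On the assumed correlations the false-positive rate is somewhat to substantially above 5%. The documents supply no value of r or g, so no single figure should be quoted as the bias of this study. The finding that adjustment costs almost no power rests on three tested predictors and f² = 0.15, the combination that reproduces N = 119.

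**What to change.** Enter MMSE as a continuous covariate in step 1 alongside activity limitation, at least in every model containing an emotion-perception measure: the one-month score for questions 1 and 3, and the concurrent one-year score for question 2. Report each model with and without it, so that readers can see how far the emotion coefficients move.

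State that the adjustment reduces confounding by cognition without removing it, because the MMSE is a brief screen with its range cut at entry. Do not claim that emotion effects are independent of cognition.

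The cost is one residual degree of freedom per model. It needs no new data and no change to the sample size.

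The two statements of the MMSE rule should also be reconciled: a score of exactly 23 fails the inclusion criterion but is not excluded under the Impairment section.

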**Methods/design:**

We aim to recruit 125 patients admitted to NHS Grampian with a confirmed diagnosis of stroke. All participants will be assessed on measures of emotion processing, social participation and activity limitation at approximately one month post stroke and again at approximately one year post stroke in order to assess change over time.

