### Aims and objectives

Therefore, this research aims to explore three different facets of emotion processing following stroke, exploring which difficulties in emotion processing occur and how these impairments impact on social participation in stroke survivors, while controlling for levels of activity limitation.

Participants will complete measures twice, at approximately one month post stroke and one year thereafter. This will allow the examination of the extent to which impairments in emotion processing are associated with social participation at both acute and chronic phases of stroke recovery. Also, by assessing participants longitudinally, direction of causation between emotion processing difficulties and social participation limitations can be explored.

The specific research questions which we will address are:

1) During the acute phase, approximately one month post-stroke, are deficits in emotion processing correlated with levels of social participation?

2) During the chronic phase, approximately one year post-stroke, are deficits in emotion processing correlated with social participation?

3) do emotion processing deficits in the acute phase of stroke predict social participation at one year post stroke which is not accounted for by activity limitation?

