## Methods

### Design

This is a predictive study with a prospective design. Measures of emotion processing and social participation administered at baseline will be used to predict participation outcome at one year post stroke.

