### Participants

A sequential cohort of 125 patients, approximately one month post stroke, will be recruited from the rehabilitation and acute stroke units, stroke outpatient clinics, and the NHS Grampian Stroke Register within Aberdeen Royal Infirmary and Woodend Hospital, Aberdeen. Potentially eligible participants are to be identified in collaboration with the acute stroke unit lead clinician.

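### The one-year regression leaves out one-month social participation, which the Design section names as a predictor, so it cannot show prediction beyond existing participation, change over time, or direction

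*Protocol article*

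**What the plan says.** Three statements of purpose depend on the repeated assessment.

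- Design section: "Measures of emotion processing and social participation administered at baseline will be used to predict participation outcome at one year post stroke".
- Aims and objectives: following patients over time means that "direction of causation between emotion processing difficulties and social participation limitations can be explored".
- Abstract, Methods/design: patients are assessed at one month and "again at approximately one year post stroke in order to assess change over time".

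The Analysis section then fixes the contents of the research question 3 model, "predicting social participation at second assessment from concurrent activity limitation in the first step and emotion processing from the acute phase of stroke entered" at the second step. It describes no other model for one-year participation and none with later emotion processing as the outcome. The Measures and Procedure sections say that the full battery, including the participation scales, is given at both visits.

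Research question 3 itself asks only for prediction that activity limitation does not explain. It does not mention participation at one month.

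**The concern.** The Design and Analysis sections describe different models for the same outcome. This is not a detail left to a fuller document, because the Analysis section says what goes into each step and the baseline value of the outcome is absent.

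The omission matters because research question 1 already anticipates that emotion processing and participation are correlated at one month. If they are, and if participation is fairly stable over the year, acute emotion processing will be associated with one-year participation even if it adds nothing to what one-month participation already tells us. The planned model compares one-year levels and gives emotion processing the credit for differences that were present at the first visit.

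A significant second step could then be read as showing that emotional deficits lead to later loss of participation. The Discussion moves in that direction when it suggests picking out such patients for intervention in the acute phase.

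**Working it through.** **1. The protocol's own figure.** The Sample size section gives "For F tests with a medium effect size", "with an error probability of 0.05 and power of 0.95", a total of 119. It states neither a numerical effect size nor the number of predictors tested. Assume f² = 0.15 (the conventional medium value for regression) and three tested predictors (the Background names three emotion constructs). With noncentrality λ = f²N = 0.15 × 119 = 17.85, power is 0.951 and the smallest adequate N is 119. The figure reproduces.

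**2. Effect of the extra covariate on that figure.** With three emotion predictors tested after activity limitation alone (four predictors in total), N = 119 gives power 0.951. After activity limitation and one-month participation (five in total), N = 119 still gives 0.951. At a fixed f² the covariate costs no sample size. The f² left after adjustment may be smaller; the protocol gives no value for it.

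**3. What persistence alone produces.** The protocol gives no correlations, so those below are assumptions. Let P1 and P2 be participation at one month and one year, E1 acute emotion processing and A2 one-year activity limitation, all standardised:

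- E1 = ρ·P1 + error
- P2 = s·P1 + 0.3·A2 + error, with A2 independent of P1 and E1

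E1 has no effect on P2 once P1 is known. In the planned model (P2 on A2, then E1):

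- coefficient of E1 = ρs
- gain in R² at step 2 = (ρs)²
- f² = (ρs)² / (1 − 0.3² − (ρs)²)
- λ = N·f², tested on F(1, N − 3)

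| ρ | s | N | ρs | R² gain | f² | λ | Step 2 significant |
|---|---|---|---|---|---|---|---|
| 0.2 | 0.4 | 100 | 0.08 | 0.0064 | 0.0071 | 0.71 | 13% |
| 0.3 | 0.5 | 119 | 0.15 | 0.0225 | 0.0254 | 3.02 | 41% |
| 0.4 | 0.6 | 119 | 0.24 | 0.0576 | 0.0676 | 8.04 | 80% |

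N = 100 corresponds to losing 20% of the 125 patients to be recruited (125 × 0.8). Simulations of the same set-up gave about 12% at the low end and 76% to 79% at the high end. With P1 in step 1, the E1 coefficient is zero by construction; the simulated rate was 4% to 5%, the nominal level.

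**4. Sensitivity to the set-up.** A second simulation used N = 119 and three emotion predictors, only one of them correlated (r) with P1. P1 and A2 correlated 0.4, and s was the overall correlation of P1 with P2. Step 2 of the planned model was significant in:

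| r | s = 0.4 | s = 0.6 | s = 0.7 |
|---|---|---|---|
| 0 | 4% | 6% | 4% |
| 0.3 | 8% | 21% | 32% |
| 0.4 | 14% | 38% | 55% |
| 0.5 | 19% | 56% | 78% |

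With P1 in step 1, every cell was at 4% to 5%. The size moves with the assumptions. The pattern does not: the rate exceeds 5% whenever a one-month association and stability coexist, and one covariate removes the excess.

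**5. The causal order reversed.** Suppose instead that emotion drives one-month participation, which then persists: P1 = ρ·E1 + error, with the same equation for P2. The correlation matrix is identical, so the planned model is significant equally often (11% to 80% when simulated) and the adjusted model again falls to about 5%. Here, though, the planned model detects a real total effect and the adjusted model removes it by conditioning on the intermediate variable. E1 and P1 are measured at the same visit, so these data cannot tell the two cases apart.

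**The case against.** The strongest reply is that the planned model answers the question the protocol asks. Research question 3 and the abstract's aim both concern prediction independent of activity limitation, and neither mentions existing participation. This stands. A reader might infer that the model cannot show any prediction of later participation, or that 12% to 80% is its false-positive rate. The documents support neither reading. In the scenarios above, acute emotion is truly associated with one-year participation given activity limitation, so rejecting the null of question 3 as worded is correct. Those rates are errors only against a different null: no contribution beyond one-month participation.

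It also stands that the planned result need not be biased away from the null, and that the adjusted model should not become the only basis for the conclusion. The protocol's rationale is that emotional impairment leads to withdrawal. If that has already happened by one month, adjustment hides part of the effect under study (step 5).

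Finally, the protocol says only that direction can be explored, and a condensed article may leave models out. This softens the point about the missing reverse model. It does not reconcile Design with Analysis, since the Analysis section itself sets out the steps.

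**Conclusion.** The point holds in limited form. The Analysis model omits a predictor that the Design section promises and that is collected on everyone. It can show an association between acute emotion processing and one-year participation given activity limitation. It cannot show prediction beyond participation already present at one month, change over time, or direction.

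Under the assumed correlations of step 3, an association that merely persists makes step 2 significant in roughly 12% to 80% of studies, against about 5% once one-month participation is included. The three-predictor version starts lower, at 8% for r = 0.3 and s = 0.4. These figures are illustrations, because the protocol gives no correlations.

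Adjustment is necessary for a claim about direction but not sufficient. Even with the reverse path examined, an observational study of this kind would not prove causation.

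**What to change.** Reconcile the Aims and objectives, Design and Analysis sections before the one-year data are analysed:

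- Keep the planned two-step model as the answer to research question 3 as worded.
- Beside it, add a hierarchical model with one-month social participation (same measure or composite as the outcome) in step 1, before acute emotion processing. Report both.
- Base any statement about prediction beyond existing participation, change or direction on the adjusted model.
- For direction, also fit the mirror model: one-year emotion processing on one-month participation, adjusting for one-month emotion processing. Otherwise delete the direction statement.

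The cost is a few lines of text and one residual degree of freedom. No new data are needed, and the 119 is unchanged at f² = 0.15 with three tested predictors. The real drawback is that the adjusted model may understate a total effect acting through one-month participation, which is why both models should be reported.
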